### Analysis

At the start of the RCT, retrospective injury data are obtained to determine equivalence in injury risk at baseline. Injury, exposure and compliance data are being collected during each month of the Australian Football season, and the outcome measures of interest are the total numbers of injuries, total exposure and overall compliance rates over the entire study period. All data will be pre-coded and double-entered into a PC database.

All analyses will be undertaken with the Stata analysis package and performed on an intention-to-treat basis with the control arm (arm 1) as the reference group. The analysis of biomechanical outcomes will take clustering of individuals within teams into account through the use of generalised estimating equations. Poisson or negative binomial regression, as appropriate, will be used to analyse injury rates with estimation of a scale parameter allowing for cluster effects.

Behavioural, attitudinal and knowledge variables will be assessed by a number of different items on a questionnaire. Responses will be scored, and the scores from different items combined to give an overall attitude score on a quasi-continuous scale. Scores will be compared preseason to postseason, and changes compared across study arms. The attitudes and behaviours of players, particularly attitudes before and after, will be compared by categorical data analysis again using generalised estimating equations to allow for cluster effects. Information about injury outcomes (ie, time away from sport and amount of treatment received) will be collected from all injured players so that the cost per injury can be calculated.

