### Recruitment

With the assistance of the parent Australian Football bodies, we identified local Australian Football leagues and their contact details of all suitable clubs/teams. The teams were randomly ordered and then invited to participate in the study until the quota was reached, with the restriction that, overall, 50% of the teams were from Ballarat and 50% from Perth. In agreeing to participate in the study at this stage, no team was informed to which arm of the RCT they would be assigned. Once teams had expressed an interest in participating in the trial, an attempt was made to recruit all players from these teams; informed consent was obtained from them. All players are aged ⩾16 years. When team recruitment was complete, whole teams were randomised to the two study arms in each state. Study teams were recruited into the larger study, even if some players did not give their informed consent for us to monitor them. This recruitment methodology has previously been used in another sports injury prevention RCT and shown to lead to unbiased recruitment of teams and players.^37^ ^41^ ^51^

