### Sample size

The intervention is being implemented during training sessions and its effects measured during games. A team consists of 18 members and a game lasts ∼100 min (four quarters of ∼20 min plus ∼5 min time added on). Over a 6-month playing season, each team has ∼20 games and so each team will contribute ∼600 game-hours of exposure to knee injury risk. We used a standard cluster randomised trial sample size calculation for comparing rates between a control arm and an intervention arm.^52^ The knee injury rate in the control arm was estimated as 20 per 1000 game-hours. This figure is based on the observation of 60.2 injuries (of all kinds) per 1000 game-hours (from data from Finch *et al*^11^) and an assumption that approximately one-third of Australian Football injuries involve the knee. To have 80% power to detect a reduction in the injury rate of 35% (ie a rate ratio of 0.65) in the intervention arm compared with controls, we would require 8.8 teams in each arm. This calculation does not take account of any clustering effects of injuries by team. From the same data,^11^ we estimate that the coefficient of variation of team injury rates will be 0.35 (ie, standard deviation of team injury rates divided by mean of team rates). Assuming that the clustering effect will be identical in the intervention arm, the number of teams required must be multiplied by 2.27, ie, 8.8×2.27 = 20 teams per study arm over the 2 years. Thus 20 teams (10 in Ballarat, 10 in Perth) will be randomly allocated to each arm of the study across the two playing seasons.

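### The Analysis section uses baseline injury data to check equivalence and compares attitude scores as changes, where prespecified baseline adjustment would give more precision for little cost

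*Protocol article*

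**What the plan says.** The Analysis section opens by stating that "retrospective injury data are obtained to determine equivalence in injury risk at baseline". It gives no other purpose for these data. Injury rates are then to be analysed by Poisson or negative binomial regression with a scale parameter for clustering; the sentence that names the model lists no covariates.

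For the attitude score the same section says: "Scores will be compared preseason to postseason, and changes compared across study arms". Generalised estimating equations are to allow for clustering.

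On the design, the Recruitment section says that "whole teams were randomised to the two study arms in each state", and the Sample size section sets 20 teams per arm, 10 in each state.

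The article does plan some adjustment. The section on potential confounding treats ground conditions as a possible confounder, partly because the trial runs in two states, and says that players' additional exercise will be adjusted for. The Compliance section says the same of contamination in the control arm. None of these places mentions the team's earlier injury experience or state itself as a model term.

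**The concern.** Teams are allocated at random, so any difference in past injury risk between arms arises by chance. Checking for equivalence therefore says little about the validity of the comparison, and with 20 teams per arm a failure to see a difference would not establish equivalence. Past injury is, however, a natural candidate to predict a team's future injury rate, and its value lies in the model.

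The change score has a similar cost. It subtracts the whole preseason score, whereas regression to the mean calls for subtracting only part of it. The comparison is valid but noisier than it needs to be.

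Precision is at stake. The sample size has no margin above 80% power, and more than half of the teams are needed because team rates vary. A covariate that explains part of that variation acts on the largest component of the required size.

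**Working it through.** **Inputs from the Sample size section.** "The knee injury rate in the control arm was estimated as 20 per 1000 game-hours"; a rate ratio of 0.65, so 13 per 1000 in the intervention arm; "600 game-hours of exposure to knee injury risk" per team; and "we estimate that the coefficient of variation of team injury rates will be 0.35". Alpha is not stated. A two-sided 5% level is assumed because it reproduces the stated 8.8 teams; a one-sided 5% level gives 6.9.

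**Reproducing the stated size.** With l0 = 0.020, l1 = 0.013, y = 600, k = 0.35 and (1.960 + 0.842)² = 7.849:

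- Without clustering: 7.849 × (0.033/600) / 0.007² = 8.81 teams per arm (stated 8.8).
- Added by clustering: 7.849 × 0.35² × (0.020² + 0.013²) / 0.007² = 11.17 teams.
- Total: 8.81 + 11.17 = 19.97 after rounding; inflation 19.97/8.81 = 2.27. Both agree with the article.

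**Effect of adjustment on the injury analysis.** Let R² be the share of between-team variance explained by the baseline injury measure and state. It is not in the documents. Replace k² by k²(1 − R²), so that teams = 8.81 + 11.17 × (1 − R²), and power with 20 teams = Φ(0.007 × √(20/v) − 1.96), where v = 0.033/600 + k²(1 − R²)(0.020² + 0.013²).

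| R² (assumed) | Teams per arm for 80% power | Power with 20 teams per arm |
|---|---|---|
| 0 | 19.97 | 80.0% |
| 0.05 | 19.4 | 81.1% |
| 0.10 | 18.9 | 82.3% |
| 0.20 | 17.7 | 84.5% |
| 0.30 | 16.6 | 86.7% |

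**What range of R² is plausible.** One earlier season gives about 0.020 × 600 = 12 knee injuries per team. If 0.35 is the true between-team coefficient of variation, the reliability of a one-season team rate is 0.35²/(0.35² + 1/12) = 0.60. R² is then the squared year-to-year correlation of true team rates times 0.60. At assumed correlations of 0.5 and 0.7 this gives 0.15 and 0.29, with power of 83% and 87%. A correlation of 1 gives a ceiling near 93%. Errors of recall would lower all of these.

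**Attitude score.** With equal preseason and postseason variance σ² and correlation rho, the change score has variance 2σ²(1 − rho) and the baseline-adjusted score σ²(1 − rho²). The ratio of adjusted to change-score variance is (1 − rho²)/[2(1 − rho)] = (1 + rho)/2:

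| rho (assumed) | Adjusted / change-score variance |
|---|---|
| 0.3 | 0.65 |
| 0.5 | 0.75 |
| 0.7 | 0.85 |
| 0.8 | 0.90 |

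The ratio is below 1 for every rho below 1. It carries over to the clustered analysis if the same correlation holds between teams and within teams.

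**The case against.** The strongest case on the other side is that this is a condensed article and that a covariate list belongs in the analysis plan. That stands for the state term. A reader might infer that state and season are ignored in the model, that the baseline injury data will be used for nothing but an equivalence check, or that precision is being thrown away. The article supports none of these. It names a model family without listing its terms, gives one purpose for the retrospective data without excluding others, and plans adjustment elsewhere. It names no significance test of baseline balance either, so a descriptive comparison would fit its wording.

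Further points also stand:

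- Comparing changes between randomised arms is valid, and the attitude score is not the outcome that sets the number of teams. The Sample size section regards its power as conservative.
- R² and rho are assumptions. At R² = 0.10 the gain is about two points of power.
- The coefficient of variation comes from a cited dataset. Whether it contains variation between states is unknown, so the gain from state alone cannot be judged.
- The gain is not free. The article does not say that the retrospective data include exposure, recalled injuries are noisy, and covariates use degrees of freedom among 40 teams.
- The Project time frame puts randomisation in January to March and attitude surveys in March to April, with interventions from March. Preseason answers may therefore follow allocation. The change score depends on the same answers, so this does not favour it over adjustment.
- The Perth laboratory measures of cutting and landing are taken in one state only, so a state term has no meaning for them.

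What the objection does not remove is that the article itself states the equivalence purpose and the comparison of changes. Those two are not silence.

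**Conclusion.** The point holds as a matter of efficiency. The stated purpose of the retrospective injury data is a weak one in a randomised trial of 40 teams, and the stated attitude analysis is less precise than adjustment for the preseason score. No figure in the article is wrong: 20 teams per arm reproduces.

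For attitude scores, adjustment would cut the variance by 25% at rho = 0.5 and by 15% at rho = 0.7, given equal variances. For injury rates, power would rise from 80% to about 82% to 87% if the covariates explain 10% to 30% of between-team variance. Both ranges rest on assumed values, and the power figures make no allowance for lost degrees of freedom.

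A reader might also infer that leaving out state would invalidate the result. It would not: omitting a stratum used in randomisation usually makes the standard error too large, which costs precision and does not inflate the type I error. Since the analysis plan may include the term, naming state is a clarification and not the repair of a proven omission.

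**What to change.** In the Analysis section:

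1. Replace the equivalence purpose with descriptive reporting of the retrospective injury data by arm.
2. Prespecify that the injury-rate model contains arm, state and the team's baseline injury measure: a rate if exposure is available for the earlier period, otherwise a count or the injury history from the preseason survey.
3. Analyse the postseason attitude score by ANCOVA on the preseason score, with state, keeping the planned allowance for clustering by team.
4. Use a state term only for outcomes measured in both states, which excludes the Perth-only biomechanics.
5. State whether the baseline measures were obtained before or after teams were allocated.

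The cost is mainly wording, since the article already plans to obtain the retrospective data and the preseason survey. The downsides are a few degrees of freedom among 40 teams, noise in recalled injuries, and the possibility that the March to April surveys fall after allocation.

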#### Intervention arm: normal training programme + intervention training programme

In addition to their usual training regimens, intervention teams are receiving a combination of skill and perturbation-type exercise training. This programme incorporates two general training modalities: (*a*) perturbation balance training and (*b*) training of technique to perform side-stepping, crossover and landing actions.^15^ ^25^ ^27^ In balance and perturbation training, the task difficulty progresses from standard proprioceptive training to performing sporting actions (eg, kicking, hand-balling) while being perturbed by the trainer. The purpose of perturbing a player is to stimulate the knee ligament mechanoreceptors, enhance voluntary movement control leading to improved joint stability, reduce ligament loads and reduce the risk of injury.^15^ ^19^ ^28^ The perturbation-training programme involves a circuit arrangement to minimise the amount of equipment required. Each circuit station includes a different item of equipment such as a mini-trampoline, aerobic steps, tilt boards, round and square wobble boards, roller boards, Dura discs and Swiss balls. There are different exercises to perform at each station, with the exercises becoming progressively harder as the player becomes more competent. Typical progressions at each station include: performing the exercises with eyes open to eyes shut; doing exercises with no external force being applied; catching and passing a ball; performing exercises while the board or person is being pushed. Most exercises progress from balancing on two feet, to balancing on one foot, to retaining balance while performing movements such as squats. All items of equipment used in the intervention training programmes are currently available from sports equipment suppliers and are relatively inexpensive (eg, wobble boards cost about AUS$40.00) and so are not prohibitive for uptake by community-based sports teams.

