### Injury and exposure details

The PDCs record the occurrence of all injuries and their circumstances, and provide injured player details for each game and training session using previously used standardised methods.^12^ ^35^ ^41^ A standardised form is used to provide a simple description of injury and notification that the player was seen by a doctor or sent to hospital. This information is obtained from the PDCs each week.

A self-report injury diagnosis will be obtained from the player after they have sought medical or other treatment for that injury. The injured player will also be asked to provide the details of the person who provided their treatment, so that their self-report information can be validated and full details of the diagnosis obtained from their medical practitioner. Medical records pertaining to injuries sustained during the games will also be obtained, and the injury descriptions reviewed by an associate investigator with medical qualifications. A medical diagnosis will be obtained and coded for each case, and this will be checked with the original notification of injury.

For each player, the amount of time spent playing Australian Football (both competition and training) over each week of the trial is recorded by the PDC. This is done in accordance with the methods previously developed for other community-based Australian Football injury studies.^12^ ^35^ ^41^ ^43^ Exposure is recorded during each training session and game.

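### The Analysis section names total injuries and total exposure, not the knee injuries per game-hour on which the trial is sized

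*Protocol article*

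**What the plan says.** Four parts of the protocol article bear on the primary rate.

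- **Hypothesis** (Research aims and hypotheses): the first hypothesis is a reduction in the rate of knee ligament injuries. The section on prevention of knee injuries defines which injuries count.
- **Sample size**: "The intervention is being implemented during training sessions and its effects measured during games". The planning rate is for the knee and per game-hour: "The knee injury rate in the control arm was estimated as 20 per 1000 game-hours". Exposure is counted the same way: "each team will contribute ∼600 game-hours of exposure to knee injury risk". No training hours enter.
- **Injury and exposure details**: injuries are recorded for each game and training session, and "the amount of time spent playing Australian Football (both competition and training) over each week of the trial is recorded by the PDC".
- **Analysis**: "the outcome measures of interest are the total numbers of injuries, total exposure and overall compliance rates over the entire study period". Injury rates are then to be modelled by Poisson or negative binomial regression. The section mentions neither the knee nor games, and names no offset. The abstract's outcome measures likewise refer only to injury in general.

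On training time, the intervention-arm section says: "In addition to their usual training regimens, intervention teams are receiving a combination of skill and perturbation-type exercise training". The control-arm section describes a sham made up of common practice and a few further exercises. Neither section gives minutes.

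**The concern.** Injuries and exposure are the two ingredients of the rates that the Analysis section goes on to model. The natural reading is therefore total injuries over total exposure, which differs from the powered quantity in two ways.

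**Numerator.** The plan assumes that about one-third of injuries involve the knee. If injuries at all sites are counted, a knee-specific effect is mixed with the other two-thirds, which the programme is not designed to change.

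**Denominator.** Training hours accrue after randomisation and can be influenced by the allocated programme. If intervention teams log more of them, at lower risk than games, the pooled rate falls in that arm without any protective effect.

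A trial sized for one rate could thus be reported on another, with much less power or with a denominator that depends on allocation.

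**Working it through.** **1. Reproduce the plan's figure.** Inputs from Sample size: control rate λ0 = 0.020 per game-hour; rate ratio 0.65, so λ1 = 0.013; y = 18 × (100/60) × 20 = 600 game-hours per team; k = 0.35; power 80%. Alpha is not stated. Two-sided 0.05 is assumed, giving (1.960 + 0.842)² = 7.849.

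- Without clustering: 7.849 × (0.033/600) / 0.007² = 8.81 teams per arm (plan: 8.8).
- With clustering: 7.849 × [0.033/600 + 0.35² × (0.020² + 0.013²)] / 0.007² = 19.97 (plan: 20). The ratio is 2.267 (plan: 2.27).

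One-sided 0.05 gives 6.9 and 15.7, which do not match. The design therefore rests on knee injuries and game-hours alone.

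**2. All-site numerator.** Sample size gives 60.2 injuries of all kinds per 1000 game-hours, of which 20 are taken as knee. A 35% knee reduction removes 7 per 1000. With other sites unchanged, the intervention rate is 53.2 and the rate ratio is 53.2/60.2 = 0.884.

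Power with 20 teams per arm, same k and y:

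- Standard error = √{[(0.0602 + 0.0532)/600 + 0.35² × (0.0602² + 0.0532²)]/20} = √{(0.000189 + 0.000791)/20} = 0.00700.
- Difference / standard error = 0.0070/0.0070 = 1.00.
- Power = Φ(1.00 − 1.96) + Φ(−1.00 − 1.96) = 0.169 + 0.002 = about 17%.

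The same formula for the knee rate gives 80.0%. If the all-site coefficient of variation were 0.20 instead of 0.35, all-site power would be about 32%.

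**3. Pooled denominator with no true effect.** With G = 600 game-hours, game rate g = 20 per 1000, usual training hours T, added hours e1 (intervention) and e0 (control), and training injury rate t:

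ratio = {[Gg + (T + e1)t]/(G + T + e1)} ÷ {[Gg + (T + e0)t]/(G + T + e0)}

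T, e1, e0 and t are not in the document. Assumed for illustration: 18 players, 2 sessions a week, 24 weeks, 1.5 h per usual session, so T = 1296 h; t from 0 to 4 per 1000 h.

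| Added minutes per session, intervention / control | Ratio with no effect |
|---|---|
| 20 / 20 | 1.00 |
| 20 / 10 | 0.93 to 0.96 |
| 10 / 0 | 0.93 to 0.96 |
| 20 / 0 | 0.87 to 0.93 |
| 30 / 0 | 0.81 to 0.90 |

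If t equals the game rate, every row is 1.00. As a guide to consequence, using the plan's own variance inputs, a spurious ratio of 0.90 would raise the two-sided rejection rate from 5% to about 11%, and 0.85 to about 20%.

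Pooling can also hide benefit. With equal hours, t = 2 and an effect in games only, a true 0.65 becomes (600 × 13 + 1296 × 2)/(600 × 20 + 1296 × 2) = 10392/14592 = 0.71.

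**4. Game-hours only.** Added training hours cannot enter the denominator, so the ratio with no effect is 1.00.

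**The case against.** The strongest reply is that the Analysis section adopts no such rate. It lists injuries, exposure and compliance as aggregates. Because the same sentence refers to monthly data collection, total may simply mean summed over the months, not all body sites or games and training pooled. No offset is named, and an article may leave that to the full protocol or analysis plan. The hypothesis and Sample size both point to knee injuries, and Sample size to games; session-level recording permits a game-hours analysis.

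Much of this stands. A reader might infer that the planned analysis divides by pooled hours and that the intervention-arm rate must therefore fall even if the programme does nothing. The document does not support that. It specifies no pooled offset. Control teams also receive extra exercises. Sample size places the intervention within training sessions, so content described as additional need not mean more net hours. The fall also requires training to be less risky than games. None of these conditions is documented.

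The reply does not remove the mismatch. The Analysis section is not silent: it names outcome measures, and they are not those of the hypothesis or the sample size. The expectation, in the section on confounding, that additional exposure will be balanced concerns players' own extra exercise, not the programme.

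It is also fair to object that a games-only primary rate excludes knee injuries sustained while doing the programme. The answer is to report those by arm as a secondary outcome.

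**Conclusion.** The inconsistency is real and should be corrected. The outcome named in the Analysis section does not match the knee ligament hypothesis or the powered rate of knee injuries per game-hour.

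The firmer consequence is in the numerator: an all-site analysis would face a rate ratio of about 0.88 with about 17% power, against 0.65 with 80%. This assumes no effect at other sites, two-sided 0.05 and a coefficient of variation of 0.35 for both rates.

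The denominator consequence is conditional. Pooling games and training leaves the rate open to influence from allocation and could favour the intervention. The illustrated range of about 0.81 to 1.00 rests entirely on assumed hours and training injury rates and is not an estimate for this trial. An automatic fall in the intervention-arm rate is not established.

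**What to change.** In the Analysis section, name the primary rate as knee injuries, as defined in the section on prevention of knee injuries, sustained in games, with log game-hours as the offset in the Poisson or negative binomial model. Report training injuries per training-hour, including knee injuries, by arm as a secondary outcome. Report all-site injuries separately, also as secondary. Do not use pooled games-plus-training hours as the denominator for the arm comparison.

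This changes wording only. Exposure is already recorded at each training session and game, and the calculation of 20 teams per arm is unaffected. The downside is that knee injuries sustained in training leave the primary count.

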To this end, biomechanical measures related to reduction in knee ligament loading will be collected from a subset of players as mentioned above. These measures will be taken while the players perform cutting and landing tasks and entail: (*a*) knee flexion angle at heel strike; (*b*) frontal plane kinematics (position and movement) trunk and pelvis position relative to foot; and (*c*) hamstrings and quadriceps muscle activation patterns. Neuromuscular measures to be taken are: (*a*) knee movement sense and position sense; (*b*) time to generate maximum knee extension and flexion torque in response to a light stimulus; (*c*) isometric knee extension and flexion strength; and (*d*) standing balance. Finally, mobility in the game situation will be assessed by (*a*) agility cone test and (*b*) reaction time to perform the cutting manoeuvres in response to a light stimulus. This battery of tests will be performed on eight players randomly selected from each team in the RCT arms in Perth only and will be taken before training starts and half way into the season. All tests will be performed in the Sports Motion Analysis Laboratory in the School of Sport Science, Exercise and Health at UWA. The cutting and landing tasks will be collected using a 12-camera Vicon 612 system with two force plates to measure kinetic data and a 16-channel telemetry electromyographic system to measure muscle activation patterns. Each participant will perform a series of trials for each task as per the procedures already developed.^14^ ^15^ ^18^ ^19^ Mathematical optimisation algorithms with a cluster marker set have already been developed to improve the repeatability of biomechanical data,^14^ ^15^ ^53^ in some cases by as much as much as 100%.^53^ The neuromuscular parameters assessed in this study will be acquired and processed using established procedures^14^ ^18^ ^32^ ^33^ that are currently used in this laboratory.

In Ballarat, we intend to use some of the neuromuscular and mobility tests selected from the battery of tests performed in Perth. These selected tests will be those that can easily be performed in the field situation. These will be: (*a*) knee movement sense and position sense; (*b*) isometric knee extension and flexion strength; (*c*) standing balance; (*d*) agility cone test. These will also be performed on eight randomly chosen people from each team and taken before training starts and about half way into the season.

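### GEE is named for laboratory outcomes that come from only 20 Perth teams; unless a small-sample correction is used, a nominal 5% test has a type I error of about 7% to 8%

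*Protocol article*

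**What the plan says.** The Analysis section of the protocol article gives the software and the analysis population ("All analyses will be undertaken with the Stata analysis package and performed on an intention-to-treat basis") and then the cluster method for this family of outcomes: "The analysis of biomechanical outcomes will take clustering of individuals within teams into account through the use of generalised estimating equations". It says nothing about the working correlation, the variance estimator, the reference distribution or any adjustment for a small number of teams.

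Two other sections fix how many teams supply the data. Under Sample size, "20 teams (10 in Ballarat, 10 in Perth) will be randomly allocated to each arm of the study". Under Biomechanical, neuromuscular and mobility outcome measures, the full laboratory battery is done on "eight players randomly selected from each team in the RCT arms in Perth only". For the other state the article says: "In Ballarat, we intend to use some of the neuromuscular and mobility tests selected from the battery of tests performed in Perth". The tests listed there are movement and position sense, isometric strength, standing balance and the agility cone test. No cutting or landing kinematics, force-plate data or electromyography are planned in Ballarat.

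**The concern.** The robust GEE variance is consistent as the number of clusters grows; adding players within a team does not help. With few teams the uncorrected variance is biased downward. Referring the statistic to a normal distribution also ignores the uncertainty in that variance. Both effects make p-values too small and intervals too narrow.

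The planning figures do not suggest that the small cluster count was noticed. The biomechanical power statement uses 20 teams per arm, so 40 clusters, and a normal approximation, while Perth supplies half that number for the laboratory measures. (The loss of power from that mismatch is a separate matter.)

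At stake are the between-arm, pre-to-post hypotheses on kinematics, knee loading and co-contraction in Research aims and hypotheses. The article intends to use such changes to explain any reduction in injury. Several laboratory measures are to be compared, so excess error on each makes it likelier that a chance difference is presented as a training adaptation.

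**Working it through.** **Inputs**
- Teams: 10 Perth teams per arm, 20 in all; 20 per arm, 40 in all, for tests done in both states (Sample size; outcome measures section).
- Players analysed per team: 6; intracluster correlation (ICC) 0.1 or 0.4 (Sample size).
- Alpha: not stated. Two-sided 5% is assumed because it reproduces the article's own figures, as follows.

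**Reproducing the article's figures**
- Design effect = 1 + (6 − 1) × ICC, which is 1.5 or 3.0. Effective players per arm = 20 × 6 / design effect = 80 or 40.
- Detectable effect = (1.960 + 0.842) × √(2 / effective n) = 0.443 SD (ICC 0.1) and 0.626 SD (ICC 0.4). The article gives 0.44 and 0.63.
- Unclustered team count = (1.960 + 0.842)² × (0.020 + 0.013) / 0.007² / 600 = 8.81. The article gives 8.8.

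**Type I error in closed form, equal team sizes**

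With *k* teams per arm, the uncorrected sandwich variance is (*k* − 1)/*k* times the unbiased variance of the difference in team means. The unbiased statistic follows a t distribution on 2*k* − 2 degrees of freedom. The uncorrected z-test therefore has size P(|t| > 1.96 × √((*k* − 1)/*k*)).

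- *k* = 10: the cut-off is 1.96 × √0.9 = 1.859 on 18 df, giving **7.9%** and coverage of 100 − 7.9 = 92.1%.
- *k* = 10, variance scaled by M/(M − 1) with M = 20 teams, normal reference: the cut-off is 1.96 × √(18/19) = 1.908, giving **7.3%**.
- *k* = 20: the cut-off is 1.96 × √0.95 = 1.910 on 38 df, giving **6.4%**.

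**Simulation check**

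20,000 null trials per setting; Gaussian outcome; exchangeable GEE; 6 players per team, or team sizes varying as binomial(8, 0.75); ICC 0.1 and 0.4. Ranges run over these settings.

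| Method | 20 teams | 40 teams |
|---|---|---|
| Uncorrected sandwich, normal | 7.6–8.2% | 6.3–6.6% |
| Model-based GEE, normal | 7.7–8.2% | 6.3–6.6% |
| Sandwich × M/(M − 1), normal | 7.0–7.4% | 6.0–6.3% |
| Uncorrected sandwich, t (teams − 2) | 6.0–6.4% | 5.5–5.8% |
| Kauermann-Carroll, t (teams − 2) | 4.8–5.3% | 4.9–5.2% |
| Mancl-DeRouen, t (teams − 2) | 3.8–4.1% | 4.4–4.7% |

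**The t reference matters.** With 20 equal teams and a normal reference, Kauermann-Carroll still gives P(|t₁₈| > 1.96) = 6.6%, and Mancl-DeRouen gives 5.4%.

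**Interval width, exact relative to uncorrected**
- 20 teams: (2.101/1.960) × √(20/18) = 1.13.
- 40 teams: (2.024/1.960) × √(40/38) = 1.06.

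**The case against.** The strongest reply is that the article says only GEE. It never says uncorrected, and an article commonly leaves the variance estimator and degrees of freedom to a full protocol or SAP, which is not shown here. A bias-corrected GEE with a t reference fits the printed sentence and would have a size of about 4% to 5%. That stands. A reader might infer that the plan commits itself to an 8% error rate, or to more false positives than it claims; the article supports neither, since it fixes no variance estimator and states no alpha.

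Four further limits also stand:
- A reader might carry the 8% over to all neuromuscular and mobility outcomes. Most of those tests are repeated in Ballarat, so they have 40 teams and about 6.4%, even if uncorrected.
- A reader might link the problem to hypothesis 2 or 3. Those relate preseason measures, or adaptations, to injury risk; what was calculated is a between-arm comparison of a continuous outcome. Injury rates are analysed by Poisson or negative binomial regression and are not affected.
- The attitude analysis also uses GEE ("again using generalised estimating equations to allow for cluster effects"), but for categorical data and with closer to 18 players per team. Nothing was computed for that case.
- The sample size counts about 600 game-hours per team per season, over two years. A reader might infer that only 5 distinct Perth teams per arm are each counted twice, which would give about 12% uncorrected. The article does not settle this, so that figure is not claimed.

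The reply does not remove the point. The article does fix the method and the cluster count, and the method performs well at that count only with an adjustment that the article does not mention.

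**Conclusion.** The concern holds in conditional form for the continuous outcomes measured only in Perth. With 20 teams, GEE with a normal reference and no proper small-sample correction has a type I error of about 7% to 8% (7.3% with the M/(M − 1) scaling, 7.9% without it). The uncorrected 95% intervals cover about 92%. A t reference alone brings the error to about 6%; a bias-corrected variance with a t reference brings it to about 4% to 5%.

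These figures assume a two-sided 5% level, Gaussian outcomes, about 6 players per team, ICC 0.1 to 0.4 and 10 distinct Perth teams per arm. They concern the mechanism hypotheses and leave the main injury comparison as it is.

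**What to change.** In the Analysis section, replace the GEE sentence for the continuous biomechanical outcomes with one of these:
- a t-test or regression on team means, with teams minus 2 degrees of freedom (exact for equal team sizes and normal outcomes); or
- a linear mixed model with a random team effect and Kenward-Roger degrees of freedom.

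If GEE is kept, specify a bias-corrected variance (Kauermann-Carroll or Mancl-DeRouen) **and** a t reference on teams minus 2 degrees of freedom, since Kauermann-Carroll with a normal reference does not restore the 5% level. State the significance level in the same place. If a correction is already specified in a document not shown, citing it settles the point.

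The cost is one sentence and no new data. Compared with uncorrected GEE, intervals become about 13% wider with 20 teams, and about 6% wider with 40 if the same method is used for the tests done in both states.
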